## Abstract

**Background:**

The increasing development and spread of artificial and assistive intelligence is opening up new areas of application not only in applied medicine but also in related fields such as continuing medical education (CME), which is part of the mandatory training program for medical doctors in Germany. This study aimed to determine whether medical laypersons can successfully conduct training courses specifically for physicians with the help of a large language model (LLM) such as ChatGPT-4. This study aims to qualitatively and quantitatively investigate the impact of using artificial intelligence (AI; specifically ChatGPT) on the acquisition of credit points in German postgraduate medical education.

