**Conclusions:**

We aim to prove that the advances in AI, especially LLMs such as ChatGPT-4 have considerable effects on medical laypersons’ ability to successfully pass CME tests. The implications that this holds on how the concept of continuous medical education requires reevaluation are yet to be contemplated.

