### Data Analysis

Sample size calculation was performed for the hypothesis that CME test results will improve from guess probability (20% correct answers, SD= 40%) to pass level (70% correct answers) with a confidence level of 1–α=.95, that is, α=.05, and a test power of 1–β=.95. Therefore, for an independent-samples, two-sided study, a sample size of at least 18 CME training courses per study arm is needed. Nonetheless, since the CME courses, as our study subjects, can be processed repeatedly using different methods without altering them or the methods, a paired-sample study is possible and preferable. This allows the same CME courses to be used in the three study arms. Although a sample size of 9 for a single-sided paired-sample study would be sufficient (only an improvement in CME test results is expected and desired by applying the study arm methods), we decided to take a conservative route and will work with 18 CME tests that will be run through all three study arms. The CME tests treated were randomly chosen from a large number of available tests. Care was taken to ensure that every high school student completed the same number of tests in each arm of the study so that confounding variables in the students were evenly distributed across the three groups. In addition, none of them would work on a single CME test twice using different methods to avoid learning effects. Together with the reuse of the CME tests in the three study arms (paired study, see above), these measures prevent any bias arising from the high school students as performing tools or the CME tests themselves as study participants. The AI-supported arms would run through within the shortest possible time and in the correct order so that unwanted training of the AI or the students during the process could be ruled out as much as possible. Statistical data analysis will be performed using the open-source software “R” (R Core Team; 2023). The data is presented as mean ± SD. Since the aim of the study is to identify differences in the percentage test results due to the different approaches in the three study arms, the Student *t* test (1-tailed) or the Mann-Whitney *U* test will be used for the pairwise comparison of means between groups, depending on the normality of the datasets. The Shapiro-Wilk test will be used to check normality. Fisher’s exact test was used to assess the independence of categorical variables. Benjamini-Hochberg adjustments of *P* values will be applied in multiple comparisons. Values of *P*<.05 were considered statistically significant.

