## Discussion

### Principal Findings

To present the influence of AI as objectively as possible, we deliberately refrained from using medically trained test participants. This allowed us to identify the pure influence of AI. Depending on the degree of success, it was necessary to determine to what extent AI can be permissible in CME training courses and what conditions or protective measures were to be imposed.

Since its launch in 2023, not only the development of ChatGPT but also its integration into the medical context increased rapidly, as shown by the ever more extensive database versions and the steadily growing number of medical publications [3-6,19-23]. However, as the capabilities of AI increase, so does the responsibility of actual intelligence to use it in the best possible way for the benefit of all without causing harm (“primum nihil nocere”). Even if the use of AI to solve examinations, whether student or specialist examinations, has already been investigated several times, there is still a knowledge gap in postgraduate teaching and its effects. Ethical, social, and above all, legal aspects, also need to be clarified.

AI has the potential to revolutionize various aspects of our lives. In medicine, its strength lies in its wide range of possible applications. However, the use of AI in education, training, and specialization must be clearly labeled, as it presents not only opportunities but also weaknesses and threats, particularly with the use of LLMs such as ChatGPT and related programs [1]. The correct use of AI in postgraduate medical education, especially LLMs, still needs to be explored and discussed.

This study aims to show that medical training tests can be successfully completed by medical laypersons using AI, which raises questions about the continued usefulness of current training programs, potential regulations to prevent misuse, and opportunities to harness AI capabilities in this context. Currently, self-study to obtain CME credits is an integral part of German postgraduate medical education. This study’s results may have the potential to influence this practice significantly.

The decision to examine ChatGPT’s results in three study arms was based on the hope of being able to compare the results obtained while gaining insight into whether the literature backgrounds of the CME were required to generate significantly superior results.

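### The stated claim is that laypersons using AI can pass CME tests, but the planned analysis only compares mean percentage scores between arms and never examines passing

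*Protocol article*

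**What the plan says.** The question is framed as one of success or passing in three places. The Abstract's Background states: "This study aimed to determine whether medical laypersons can successfully conduct training courses specifically for physicians". The Abstract's Conclusions say that the study intends to prove that large language models "have considerable effects on medical laypersons’ ability to successfully pass CME tests". The Discussion (Principal Findings) adds: "This study aims to show that medical training tests can be successfully completed by medical laypersons using AI".

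Methods, Data Analysis, states the aim differently: "the aim of the study is to identify differences in the percentage test results due to the different approaches". The tests follow from that wording: a one-tailed t test or Mann-Whitney test for pairwise comparison of means, with data shown as mean ± SD and Benjamini-Hochberg adjustment.

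The 70% pass level appears once, in the sample size hypothesis that "CME test results will improve from guess probability (20% correct answers, SD= 40%) to pass level (70% correct answers").

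The only categorical method is given as "Fisher’s exact test was used to assess the independence of categorical variables", with no variables named. The same section says that the same 18 CME tests go through all three arms as a paired study.

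**The concern.** Whether a given CME test reaches the pass level is a yes/no result for that test. The headline claim is about that result, but the analysis is about the average score. A difference between two averages is silent on whether either arm reaches 70%, and an average at or above 70% does not say how many individual tests reached it.

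If the plan is followed as written, the study could report a significant benefit of ChatGPT-4 and conclude that laypersons can pass, without any planned analysis having addressed passing. The Discussion proposes to draw regulatory consequences for CME from the degree of success, so the gap affects the conclusion that matters most. If pass counts are added only after the scores have been seen, the definition and method will have been chosen with the data in view.

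**Working it through.** **1. Reproduce the plan's own figure.** Inputs from Data Analysis: 20% to 70% correct, SD 40%, "α=.05, and a test power of 1–β=.95". The standardised difference is d = (70 − 20)/40 = 1.25.
- Independent samples, two-sided, noncentral t with 2n − 2 df and noncentrality d√(n/2): n = 17 gives power .942 and n = 18 gives .954. The stated 18 is reproduced.
- Paired, one-sided, noncentral t with n − 1 df and noncentrality d√n, taking 40% as the SD of the differences: n = 8 gives .936 and n = 9 gives .961. The stated 9 is reproduced.

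The sample size is therefore sound on its own terms, and those terms are mean scores only.

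**2. A difference in means can be significant with neither mean at the pass level.** Assumed figures: means 60% and 40%, SD 20 in each arm, 18 tests per arm, unpaired.
t = (60 − 40) / (20 × √(2/18)) = 20/6.67 = 3.0 on 34 df, two-sided P = .005 (half that one-tailed).

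**3. A mean at the pass level is not the same as passing.** The documents do not give the number of questions per test. Assume m independent questions, each correct with probability p. The chance of passing is P(X ≥ 0.7m) with X ~ Binomial(m, p).

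| Questions | Needed | p | Chance of passing |
|---|---|---|---|
| 10 | 7 | .70 | .650 |
| 10 | 7 | .75 | .776 |
| 10 | 7 | .80 | .879 |
| 10 | 7 | .90 | .987 |
| 5 | 4 | .70 | .528 |

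For m = 10 and p = .70: .267 + .233 + .121 + .028 = .650 (sum of the rounded terms .649).

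**4. What 18 tests can say about passing directly.** Exact (Clopper-Pearson) 95% CIs:
- 18/18 passed: 81.5% to 100%
- 15/18: 59% to 96%
- 14/18: 52% to 94%
- 12/18: 41% to 87%

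**5. If arms are compared on pass/fail.** Fisher's test sees only the margins; exact McNemar uses the discordant pairs (two-sided P = 2 × P(Bin(b + c, ½) ≤ min(b, c))). Assumed outcomes:

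| Passed | Discordant pairs | Fisher P | McNemar P |
|---|---|---|---|
| 16/18 v 10/18 | 6:0 | .060 | .031 |
| 12/18 v 6/18 | 6:0 | .094 | .031 |
| 12/18 v 6/18 | 12:6 | .094 | .238 |

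For 6:0, McNemar P = 2 × (½)⁶ = .031.

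**6. Direction of Fisher's error.** Simulation of 18 null pairs (20,000 runs per setting, two-sided .05, pass rates .5, .7 and .9, latent within-test correlation 0 to .9): the false-positive rate was at most about .03 and fell to about 0 as correlation rose. Fisher's test becomes conservative.

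**7. Power of the pass/fail comparison**, same set-up, assumed pass rates .8 v .4:

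| Latent correlation | Fisher | Exact McNemar |
|---|---|---|
| 0 | .61 | .55 |
| .3 | .62 | .62 |
| .6 | .63 | .72 |
| .9 | .64 | .79 |

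For .9 v .5, Fisher has .67 to .70 and McNemar .62 to .79. All these values lie below the .95 planned for scores.

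**The case against.** The strongest reply is that a score is a legitimate outcome and carries more information than pass/fail. The Interventions section gives the purpose of the three arms as finding differences in the ability to solve the tests and in time taken. The Discussion asks whether entering the course text improves results. The score comparison answers these questions, and dichotomising costs power. All of this stands, and it is why the score comparison should be kept. It does not remove the mismatch, because the pass claim in the Abstract and Discussion is still left without an analysis.

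It may also be said that the plan never equates a mean of 70% with every test being passed, and that the 65% figure depends on 10 questions and a success probability exactly at the threshold. That is fair: at .80 the figure is 88% and at .90 it is 99%. The 65% illustrates the gap and does not predict the result.

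Two stronger readings are tempting and are not supported. A reader might infer that pass/fail is to be tested by Fisher's exact test. The article names no variables for that test, so this is only a possibility. A reader might also infer that Fisher's test would produce false positives here. An outcome such as 18/18 v 13/18 (Fisher P = .045, exact McNemar P = .063) seems to suggest it, but five discordant pairs cannot give an exact McNemar P below .0625, so the example shows the coarseness of that test. Under non-negative within-test correlation, Fisher's test errs towards missing differences.

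**Conclusion.** The point holds as an internal mismatch. The stated claim is about passing at 70%, while the stated analysis concerns differences in mean scores, and no planned result would show that tests are passed. This is not detail left to a fuller document, because Data Analysis itself states the aim from which it selects its tests, and that aim differs from the one in the Abstract and Discussion.

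The size of the gap depends on assumptions that the article does not settle. With 10 independent questions, a true per-question probability of .70 to .90 corresponds to 65% to 99% of tests passed. With 18 tests, even a perfect record leaves a lower confidence limit of 81.5%.

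The score comparison and its sample size are not undermined. The remark on Fisher's test is conditional: if it is used to compare arms, it ignores the pairing and loses sensitivity when results on the same test are positively correlated. The change should be made, but the design does not depend on it.

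**What to change.** - Define test passed (at least 70% correct) as a named key outcome for each CME test in each arm.
- Report the number of the 18 tests passed per arm with an exact 95% CI, and base any statement that laypersons can pass on this result.
- Keep the percentage score comparison alongside it.
- If arms are compared on pass/fail, use the exact McNemar test within the planned Benjamini-Hochberg adjustment. State which variables Fisher's exact test is for, and do not use it between arms.

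The cost is a few sentences. Pass/fail follows from scores already being collected, and the Results section describes data acquisition as still under way in October 2024 with analysis to follow, so at that stage the outcome could be fixed before analysis. The downside is that the pass/fail comparison has less power than the score comparison, and exact McNemar gains over Fisher only when within-test correlation is moderate or high. The per-arm count with its CI needs no between-arm test to answer the headline question.

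### The design is paired by CME test, but the plan names an independent-samples test (Mann-Whitney U) and a t test not specified as paired; the likely cost is power for smaller arm contrasts

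*Protocol article*

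**What the plan says.** All of this stands in the Data Analysis section of the protocol article.

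- **Design.** The sample size is first worked out for unrelated arms: "for an independent-samples, two-sided study, a sample size of at least 18 CME training courses per study arm is needed". The article then moves to another design: "a paired-sample study is possible and preferable. This allows the same CME courses to be used in the three study arms". It commits to 18 CME tests, each processed in all three arms, and calls this a paired study again when arguing that bias is prevented. The Study Participants section agrees that the CME tests, not the students, are the units of study.
- **Analysis.** The arms are compared two at a time: "the Student *t* test (1-tailed) or the Mann-Whitney *U* test will be used for the pairwise comparison of means between groups". The choice between the two tests is made "depending on the normality of the datasets", using the Shapiro-Wilk test, and P values are adjusted by Benjamini-Hochberg.
- **What is not named.** No paired t test, Wilcoxon signed-rank test, Friedman test or mixed model appears in the article. The word pairwise in the analysis sentence refers to pairs of arms, not to matching by CME test.

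**The concern.** Each CME test supplies one score per arm, so the three sets of 18 scores are matched. An easy test is likely to score high in every arm and a hard one low. A paired analysis removes that shared difficulty by working on the 18 within-test differences. An independent-samples analysis leaves it in the error term.

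Mann-Whitney U assumes two unrelated samples; its counterpart for matched data is the Wilcoxon signed-rank test. The normality check has the same weakness. A paired t test relies on the distribution of the differences, whereas the article speaks only of the datasets.

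At stake is a missed difference. The Discussion says that the three arms were chosen partly to learn whether the CME literature is needed for better results, which is the comparison of All-In with Just Answers. A null result there, from a test that discards the matching, could be misread as showing that the source text adds nothing.

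**Working it through.** **Inputs from the Data Analysis section**

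- Reference level and SD: "guess probability (20% correct answers, SD= 40" (percentage points)
- Target: "to pass level (70% correct answers", so the planned difference is 70 − 20 = 50 points and d = 50/40 = 1.25
- Level: "with a confidence level of 1–α=.95, that is, α=.05"
- Power: "a test power of 1–β=.95"
- n = 18 CME tests in each arm

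**Assumptions, not in the document**

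- Within-test correlation ρ of 0.3, 0.5 or 0.7
- A 20-point arm difference as an example of a smaller contrast
- Normal scores with SD 40 in both arms
- One-sided testing at 0.05, before the Benjamini-Hochberg adjustment

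**Step 1: the plan's own figures.** For independent samples, two-sided, the noncentrality is d√(n/2) = 1.25 × √9 = 3.75 on 34 df, and the exact power is 0.954. The stated 18 per arm reproduces. For a paired one-sided test with SD of differences 40 and n = 9, the noncentrality is d√n = 1.25 × 3 = 3.75 on 8 df, and the power is 0.961. The stated 9 reproduces. The sample sizes are not in error.

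**Step 2: the correlation that the figure of 9 implies.** SD of differences = 40√(2(1 − ρ)). This equals 40 only when ρ = 0.5. If each arm has SD 40, the plan's paired calculation therefore uses ρ = 0.5, whether or not that was intended.

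**Step 3: standard error of the difference between two arm means.** The independent formula gives 40√(2/18) = 13.3 points whatever ρ is. The true value is 40√(2(1 − ρ)/18): 11.2 at ρ = 0.3, 9.4 at 0.5 and 7.3 at 0.7. The independent analysis overstates the standard error whenever ρ is positive.

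**Step 4: consequences, by simulation of 18 correlated pairs.**

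| ρ | Type I error, independent t | Type I error, paired t | Power for 20 points, independent t | Power for 20 points, paired t |
|---|---|---|---|---|
| 0 | 5.0% | 5.0% | 0.43 | 0.42 |
| 0.3 | 2.6% | 5.0% | 0.42 | 0.53 |
| 0.5 | 1.2% | 5.0% | 0.41 | 0.65 |
| 0.7 | 0.3% | 5.0% | 0.39 | 0.84 |

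The rank tests behave alike. At ρ = 0.5, one-sided Mann-Whitney has a type I error of about 1.3% and power of 0.39 for 20 points, against 0.64 for the Wilcoxon signed-rank test.

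**Step 5: the planned 50 points.** One-sided power at ρ = 0 is 0.979 (independent t) and 0.975 (paired t). At ρ = 0.5 it is 0.997 and above 0.999.

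**The case against.** - **The t test may be meant as paired.** The term Student t test covers the paired version too, and the section calls the study paired. This stands in part: the mismatch is certain only for Mann-Whitney U. The t test is not labelled paired, however, and it stands beside Mann-Whitney and the words between groups, so independent samples is the natural reading. Likewise, the article does not say outright that normality is checked on the raw arm scores.
- **The error is on the safe side.** This stands. A reader might infer that the wrong test inflates false positives. With positive correlation it does the reverse, and a significant result would remain credible. Type I error exceeds 5% only if the correlation is negative (about 7.6% for the independent t at ρ = −0.3), which reuse of the same tests makes unlikely.
- **The study is powered without pairing.** This stands for the stated hypothesis: 18 per arm was sized for independent samples. But 50 points is the distance from guessing to passing, not an expected gap between the two ChatGPT arms, and for smaller gaps the loss is material.
- **Reuse of the tests still prevents bias.** This stands. A reader might conclude that the purpose of reusing the tests is lost. It is not: every arm gets the same 18 tests, so difficulty is balanced by design, and the mean difference is the same with or without pairing. Only precision is lost.

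**Conclusion.** The point holds in a limited form and should be fixed. The article states a paired design but names one test that does not fit it and another that it leaves unspecified. This is a mismatch within one section, not a detail left to a document that is not shown.

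The effect is loss of power. Over the assumed correlations of 0.3 to 0.7, power for a 20-point contrast falls short by 0.53 − 0.42 = 0.11 to 0.84 − 0.39 = 0.45. At the 0.5 implied by the plan's own paired sample size, the shortfall is 0.65 − 0.41 = 0.24. These figures rest on the assumed correlation, the assumed 20 points and normal scores with the plan's SD of 40; real scores are bounded percentages. At zero correlation the two t tests are nearly equivalent, and at the planned 50 points the choice hardly matters.

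**What to change.** Replace the analysis sentence so that each comparison of two arms uses the 18 within-CME-test differences: a paired t test or, if those differences are not normal, the Wilcoxon signed-rank test. State that Shapiro-Wilk is applied to the differences.

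The Results section gives six students for 18 × 3 = 54 results, so each contributes several, and no student works on the same CME test twice. The scores within a pair therefore come from different students, which tests on the 18 differences do not model. A mixed model with CME-test and student effects can serve as a sensitivity analysis.

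The cost is a sentence or two in the plan and the paired option in R. No new data are needed. Make the change before the analysis is run, so that the choice between paired and unpaired tests is not made with the results in view.

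### The analysis targets mean scores, but a normality check can switch it to the Mann-Whitney U test, which does not compare means when the arms differ in shape

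*Protocol article*

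**What the plan says.** All the relevant text is in the Data Analysis section of the protocol article.

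- **Aim:** "the aim of the study is to identify differences in the percentage test results due to the different approaches in the three study arms".
- **Summary statistic:** "The data is presented as mean ± SD".
- **Basis of the sample size:** a shift in mean score from "guess probability (20% correct answers, SD= 40%) to pass level (70% correct answers"), with "a test power of 1–β=.95".
- **Test:** the Student "test (1-tailed) or the Mann-Whitney" U "test will be used for the pairwise comparison of means between groups, depending on the normality of the datasets".
- **Switch between the two:** "The Shapiro-Wilk test will be used to check normality".

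The same section says that the 18 CME tests pass through all three arms and that the paired design is preferred. It applies a Benjamini-Hochberg adjustment to multiple comparisons. It does not say whether normality is checked on the arms or on within-test differences, whether one choice covers all three contrasts, or whether Mann-Whitney is one- or two-sided.

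**The concern.** The aim, the reported summary and the power calculation all concern means. One branch of the test rule does not. Mann-Whitney asks whether a score from one arm tends to exceed a score from the other. That becomes a question about means only when the two distributions have the same shape and differ by a shift, and the section makes no such assumption. It still describes both branches as comparing means.

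Two things are at stake. The data decide which hypothesis is tested. And a report could show equal means, or even a lower mean, beside a significant advantage. The Benjamini-Hochberg step cannot repair this, because the P values it receives address a different hypothesis.

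**Working it through.** **1. The plan's own figures.** Difference 70 − 20 = 50 points, SD 40, so d = 50/40 = 1.25. The normal approximation gives n = 2(1.960 + 1.645)²/1.25² = 16.6, or 17 per arm. The noncentral-t solution is 17.65, or 18 per arm, with power .954. The one-sided paired calculation, with SD of differences 40, gives 8.49, or 9. Both stated sizes reproduce, and both rest on t tests of means.

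**2. How often the rank branch is used.** Assumptions: 18 tests per arm, 10 questions per test, Shapiro-Wilk at .05 on each arm, Mann-Whitney if either arm is rejected. With a dispersed (beta-binomial) arm against a binomial arm of the same mean, at least one arm fails the check in 85-100% of runs when the mean is 80-90%. At a mean of 70% the figure is 62-82%.

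**3. A worked example with equal means.** Arm A has 15 scores of 100 and 3 of 40. Arm B has 3 of 80, 12 of 90 and 3 of 100.

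- Means: A = (1500 + 120)/18 = 90.0; B = (240 + 1080 + 300)/18 = 90.0.
- Shapiro-Wilk: P = 3×10⁻⁷ for A and .0005 for B, so the rule selects Mann-Whitney.
- U = 15 × (15 + 3/2) = 247.5 out of 18 × 18 = 324 pairs, or 76%.
- One-sided P = .0016 (two-sided .0033). The t test gives one-sided P = .50.

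Now change one more score in A from 100 to 40. A's mean becomes (1400 + 160)/18 = 86.7, below B's 90.0. U = 14 × 16.5 = 231, and the one-sided P is .0096. That is under .05/3 = .0167, so it would survive Benjamini-Hochberg over three contrasts even as the only small P value.

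**4. Error rate under equal true means of 80%.** Assumptions as in step 2, arms drawn independently, level .05. The shapes are assumed and are not in the article. Each mixture has mean 80%: .8 × .95 + .2 × .20 = .80 and .8 × .90 + .2 × .40 = .80. Brackets give the range for 5 to 20 questions per test.

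| More dispersed arm v other arm | Rule favours the dispersed arm, one-tailed | Rule, two-sided |
|---|---|---|
| .95 on 80% of tests, .20 on the rest, v SD 10 points | 43% (26-64%) | 31% |
| .90 on 80% of tests, .40 on the rest, v SD 10 points | 15% (10-24%) | 9% |
| SD 25 v 5 points | 30% (18-40%) | 22% |
| SD 20 v 10 points | 13% (10-18%) | 8% |
| Identical distributions | about 5% | about 5% |

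A paired t test on the same four unequal-shape scenarios rejects in about 6-8% one-tailed. If the hoped-for arm is the less dispersed one, the rule's one-tailed rate falls to 0.1-2%.

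**5. Effect of pairing.** In the first scenario a signed-rank test gives 15% one-tailed and 10% two-sided, so part of the 43% comes from using an unpaired rank test, and part remains after pairing. If scores correlate within tests (latent correlation .8, assumed), the SD 20 v 10 case falls to 8% one-tailed and 3.7% two-sided. The .90/.40 case falls to 11.5% and 6.6%. The two more extreme cases barely move.

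**The case against.** The strongest objection is that the size and direction come from shapes the article does not give. Its only planning figures are 20%, 70% and SD 40. High-scoring arms, mixtures and unequal spreads are assumptions. Letting a normality test guide the choice of test is a common convention, calling the result a comparison of means may be loose wording in a condensed article, and readers would see the means in any case. The proposed paired t test is not exact either: with more skewed arms, at a mean of 90%, it reached 10.8% one-tailed.

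Most of this stands as a limit on the size. It does not remove the point. The target, both tests and the switch are all stated in the text, so this is not a detail left to another document.

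Three stronger readings are tempting, and the article supports none of them:

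- **That the error favours the AI arms.** It favours whichever arm is more dispersed. The article does not say which that will be, and a keyword-search control could be the erratic one.
- **That normality is checked arm by arm and pair by pair, so the three contrasts will be tested by different methods.** The wording does not settle this. A single choice for all contrasts is equally possible.
- **That Mann-Whitney will be one-tailed.** The one-tailed label is attached to the t test only, which is why both sets of rates are given above.

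**Conclusion.** The point holds as a mismatch between the stated target and one branch of the stated test rule. If an arm scores high, that branch is likely to be the one used. It can then give a significant result that contradicts the reported means, as the worked example shows without any simulation.

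The size is conditional. With equal means of 80%, 10 questions per test, independent arms and per-arm checking, the rule falsely favours the more dispersed arm in about 13-43% of trials one-tailed (8-31% two-sided). It is conservative in the opposite configuration and correct when shapes are equal. The milder cases shrink further if scores correlate within tests. The direction cannot be stated in advance, and some of the excess belongs to the separate problem of unpaired tests in a paired design. This should be corrected before the analysis, but it does not show that the trial is biased towards AI.

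**What to change.** Delete the Shapiro-Wilk gate. Before the analysis, which the Results section expects to end in December 2024, fix one procedure for all three contrasts: the mean within-test difference in percentage score, its 95% confidence interval, and a paired t test or a studentised sign-flip permutation test, whatever the distributions look like. State that the level of the t test is approximate with 18 tests. Keep a paired rank test only as a labelled sensitivity analysis, and do not describe it as comparing means.

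The cost is two sentences in Data Analysis and a few lines of R code, with no new data. The downside is slightly lower power than a rank test when the arms share a skewed shape.
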